## 11.2 Recording Adverse Events

All adverse events will be recorded in the medical records in the first instance with clinical symptoms and accompanied with a simple, brief description of the event, including dates as appropriate.

All adverse events will be recorded and assessed for seriousness in the medical records and CRF following consent (First Participant First Visit - FPFV) until (Last Participant Last Visit - LPLV), visit 7 and if the participant consents to the optional LP at visit 7, day 279 they will receive a telephone call (telephone call 12) to record AEs within 5 days of this visit.

## 11.3 Assessments of Adverse Events

Each adverse event will be assessed for the following criteria:

### 11.4 Severity

| Category | Definition |
|----------|------------|
|----------|------------|

|                 |                                                                                                                                                                     |
|-----------------|---------------------------------------------------------------------------------------------------------------------------------------------------------------------|
| Mild     | The adverse event does not interfere with the participant's daily routine, and does not require intervention; it causes slight discomfort                           |
| Moderate | The adverse event interferes with some aspects of the participant's routine, or requires intervention, but is not damaging to health; it causes moderate discomfort |
| Severe   | The adverse event results in alteration, discomfort or disability which is clearly damaging to health                                                               |

## 11.5 Causality

The assessment of relationship of adverse events to the administration of IMP is a clinical decision based on all available information at the time of the completion of the case report form. The following categories will be used to define the causality of the adverse event:

| Category | Definition                                                                                                                                                                                                                                                                                         |
|-----------------|-----------------------------------------------------------------------------------------------------------------------------------------------------------------------------------------------------------------------------------------------------------------------------------------------------------|
| Definitely:     | There is clear evidence to suggest a causal relationship, and other possible contributing factors can be ruled out.                                                                                                                                                                                       |
| Probably:       | There is evidence to suggest a causal relationship, and the influence of other factors is unlikely                                                                                                                                                                                                        |
| Possibly        | There is some evidence to suggest a causal relationship (e.g. the event occurred within a reasonable time after administration of the trial medication). However, the influence of other factors may have contributed to the event (e.g. the participant's clinical condition, other concomitant events). |
| Unlikely        | There is little evidence to suggest there is a causal relationship (e.g. the event did not occur within a reasonable time after administration of the trial medication). There is another reasonable explanation for the event (e.g. the participant's clinical condition, other concomitant treatments). |
| Not related     | There is no evidence of any causal relationship.                                                                                                                                                                                                                                                          |
| Not Assessable  | Unable to assess on information available.                                                                                                                                                                                                                                                                |

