### **10.11 IMP Discontinuations**

Based on the known good safety profile of ambroxol no clinical significant adverse reactions are expected in this study. However individual participants may be discontinued from treatment at any time during the study (alternatively the study may be terminated prematurely) in the events of unexpected, significant or unacceptable adverse event such that, in the opinion of Investigators would put them or other trial participant safety at risk.

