### **10.12 Participant Stopping Criteria**

The stopping criteria refer to a participant stopping administration of the IMP. The withdrawal of a participant from the study may include the following reasons:

- Participants withdrawal of consent
- Non-compliance with the protocol
- Occurrence of an AE or change in medical status or an incidental finding that leads the Investigator concerned about the participant's welfare
- Pregnancy during the study
- Inability to continue, loss to follow-up
- The termination of the study by the Sponsor

If a participant is withdrawn from the study, they will be asked to undergo the early termination visit (visit 7, day 279) study procedures if applicable.

If enrolled participants prematurely discontinue the study or do not comply with the protocol, additional participants may be enrolled as replacement participants and assigned to the same treatment sequence at the discretion of the Principal Investigator. A maximum of two GBA positive and two GBA negative participants may be enrolled as replacement participants.

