### **10.13 Intra-participant Dose Escalation Stopping Criteria**

Dose escalation will be halted and reviewed by the TMG if:

- a serious adverse event (SAE) occurs in 1 or more participants receiving ambroxol that is considered at least possibly related to study drug;
- two or more severe adverse events occur in a group for subjects receiving ambroxol that are considered at least possibly related to study drug;
- A formal decision will be sent to the sponsor to restart dose escalation (if deemed appropriate). A participant already on the dose escalation regime will continue if no adverse reactions have occurred.

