### 11.1 Definitions

| Term                                                    | Definition                                                                                                                                                                                                                                                                   |
|---------------------------------------------------------|------------------------------------------------------------------------------------------------------------------------------------------------------------------------------------------------------------------------------------------------------------------------------|
| Adverse Event (AE)                               | Any untoward medical occurrence in a patient or clinical trial subject administered a medicinal product and which does not necessarily have a causal relationship with this treatment.                                                                                       |
| Adverse Reaction (AR)                            | Any untoward and unintended response in a participant to an investigational medicinal product which is related to any dose administered to that participant.

This includes medication errors, uses outside of protocol (including misuse and abuse of product) |
| Serious Adverse Event (SAE),
Serious Adverse | Any adverse event, adverse reaction or unexpected adverse reaction, respectively, that:                                                                                                                                                                                      |

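### As 10.13 and 11.5 are written, an SAE or severe adverse event rated Not Assessable for causality does not trigger the mandatory dose-escalation halt

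*Protocol*

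**What the plan says.** Section 10.13 of the protocol halts dose escalation, with TMG review, under either of two triggers. The first is that "a serious adverse event (SAE) occurs in 1 or more participants receiving ambroxol that is considered at least possibly related to study drug". The second is that "two or more severe adverse events occur in a group for subjects receiving ambroxol that are considered at least possibly related to study drug". Restarting needs a formal decision sent to the sponsor. The section also has a continuation clause: "A participant already on the dose escalation regime will continue if no adverse reactions have occurred". Section 11.1 defines an adverse reaction as an untoward and unintended response "which is related to any dose administered to that participant".

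Section 11.5 supplies the causality scale: Definitely, Probably, Possibly, Unlikely, Not related and Not Assessable. The entry for Possibly opens "There is some evidence to suggest a causal relationship (e.g. the event occurred within a reasonable time after administration of the trial medication" and accepts that other factors may have contributed. The entry for Not Assessable reads "Unable to assess on information available". The rating rests on what is known when the case report form is completed.

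Other protections do not depend on causality. Under 10.11, "individual participants may be discontinued from treatment at any time during the study". Section 10.12 lists as a stopping reason "Occurrence of an AE or change in medical status or an incidental finding that leads the Investigator concerned" about the participant's welfare. The risk table in Section 3 lets the PI withdraw a participant after an SAE. Section 11.9 sends every SAE to the sponsor within 24 hours, and 11.13 provides for urgent safety measures. Section 11.16 takes a participant out of the study for a clinically significant finding on a clinical investigation.

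**The concern.** The scale contains a rating that the stopping rule does not deal with. Both triggers in 10.13 need a judgement that the drug is at least possibly the cause, and Possibly itself needs some evidence. A rater who selects Not Assessable has made no such judgement. Following the two sections as written, an unexplained serious event therefore leaves the only mandatory escalation brake unused.

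This matters in this design because stepping up is the default. Participants receive three months' supply on day 1 and raise their own dose on days 8, 15, 22 and 29, so someone has to act to stop the next step. Section 2.2 justifies the escalation scheme partly as protection against unreported or idiosyncratic effects, and these can be hard to attribute when first reported.

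**Working it through.** No event rate or rate of Not Assessable ratings is given, so there is no planned figure to reproduce. The check is a mapping of the scale in 11.5 onto the rule in 10.13, followed by simple arithmetic on the dosing table in 10.7 and the visit schedule in Section 9 and Appendix 1.

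**1. Ratings against triggers**

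| Rating in 11.5 | At least possibly related? | One SAE | Severe AE counts towards two? |
|---|---|---|---|
| Definitely, Probably, Possibly | Yes | Halt | Yes |
| Unlikely, Not related | No | No halt | No |
| Not Assessable | Not stated; as written, no | No halt | No |

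For a single SAE the rating alone decides whether the halt applies.

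**2. Severe events**

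The trigger needs a count of at least 2.
- One event rated Possibly and one Not Assessable: count = 1 + 0 = 1, no halt. If Not Assessable counted: 1 + 1 = 2, halt.
- A single severe, non-serious event: the count is at most 1 under any rating, so the rating changes nothing on its own.

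**3. Continuation clause**

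Taking the clause to refer to the participant's own reactions, a participant continues if none has occurred, and 11.1 makes relatedness part of the definition of a reaction. A Not Assessable event is then not counted as a reaction. So even when someone else's event has triggered the halt, the participant with the unexplained event may go on stepping up.

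**4. What lies ahead for the affected participant**

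For an event in stage i, step-ups left = 5 − i, and rise to the top dose = 1260 ÷ current daily dose.

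| Stage | Daily dose (mg) | Step-ups left | Rise to 1260 mg |
|---|---|---|---|
| 1 | 180 | 4 | 1260/180 = 7.0 |
| 2 | 360 | 3 | 1260/360 = 3.5 |
| 3 | 540 | 2 | 1260/540 = 2.3 |
| 4 | 900 | 1 | 1260/900 = 1.4 |
| 5 | 1260 | 0 | 1.0 |

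These describe the planned schedule if nobody intervenes. They are not an estimate of expected harm.

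**5. Scheduled contact**

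Visit 4 falls on days 9–11 and visit 5 on day 93 ± 14. The gap between them runs from (93 − 14) − 11 = 68 days to (93 + 14) − 9 = 98 days, and it contains the step-ups on days 15, 22 and 29. Adverse-event telephone calls are scheduled within it on days 12–14, 16–18, 19–21, 23–25, 26–28 and 30–32, and 9.24 allows unscheduled visits.

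**6. Search for a default**

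No sentence in the protocol text treats Not Assessable as related or unrelated. Section 11 refers to a sponsor SOP for collecting, recording and reporting adverse events, and 11.9 to an SAE flow chart. Neither can be seen here.

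**The case against.** The strongest reply is that this is silence, not a misstatement. Section 10.13 does not cite the scale in 11.5, and a clinician who cannot rule out the drug could treat an event as at least possibly related. That reading is available, but the protocol does not require it, and a halt rule should not depend on which reading the rater prefers.

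The second reply is that few events would fall in the gap. With dosing three times daily, most on-treatment events occur within a reasonable time of a dose and fit the example under Possibly. Most SAEs also involve an admission or other care that leaves records. This stands, and it is the main reason for the low severity.

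The third reply is that other safeguards would act. It is fair to list them, and 11.16 even uses mandatory wording without a causality test. But it covers findings on investigations and removes one participant only; it does not halt escalation or call for TMG review. The PI's options in Section 3, 10.11 and 10.12 are discretionary, the 24-hour report informs the sponsor, and urgent safety measures depend on someone deciding to take them. Section 2.2 also presents the escalation criteria as additional to the other stopping rules, so they were never meant to stand alone.

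The fourth reply is that the TMG consists of the CI/PI and the research team, so a forced review returns the event largely to those who could not assess it. That limits the gain from review. It does not remove the value of a pause while information is gathered.

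Finally, the unseen SOP or flow chart may already hold a default. If so, the change amounts to writing it into the rule that uses it.

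**Conclusion.** The gap is real in the protocol text, narrow, and of low severity. Read as written, a Not Assessable SAE triggers no mandatory halt, a Not Assessable severe event does not count towards the required two, and neither bars the affected participant from the next step-up. Its frequency cannot be stated from the document and is probably low. When it does occur, the participant directly affected has between one and four planned step-ups left if the event falls in stages 1 to 4.

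A reader might infer three stronger things that the document does not support:
- That such a participant would be escalated regardless. The investigator can stop dosing at any time, and adverse events are reviewed by telephone before each step-up.
- That other participants are left exposed. Section 10.13 lets those already escalating without adverse reactions continue even when the halt applies. It halts escalation and does not say that new participants stop entering, so no count of people protected by the halt can be derived.
- That the sponsor has no default for unassessable causality. Only its absence from the protocol text can be established.

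The conclusion assumes that relatedness in 10.13 is judged on the 11.5 scale, the only one in the protocol, and that the unseen SOP and flow chart do not already settle the matter.

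**What to change.** Add one sentence to 10.13: an SAE or severe adverse event rated Not Assessable counts as at least possibly related until it is re-rated, for both triggers and for the continuation clause, so that the affected participant does not step up in the meantime. Add one sentence to 11.5: a Not Assessable rating is revisited when further information arrives. If the SOP or flow chart already holds a default, the new wording should match it.

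This is a cheap improvement, needing two sentences in a protocol amendment. The downside is an occasional TMG review or pause for an event later judged unrelated.

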## 11.6 Expectedness

| Category          | Definition                                                                                                                                       |
|-------------------|--------------------------------------------------------------------------------------------------------------------------------------------------|
| Expected   | An adverse event which is consistent with the information about the IMP listed in section 4.8 of the SmPC (Reference Safety Information - RSI)   |
| Unexpected | An adverse event which is not consistent with the information (RSI) about the IMP listed in the Investigator Brochure (or SmPC if Licensed IMP)* |

\* this includes listed events that are more frequently reported or more severe than previously reported.

The reference document to be used to assess expectedness against the IMP is highlighted in the SmPC for Ambrosan (Ambroxol) (Marketing Authorisation holders PRO.MED.CS Praha a.s., [name])

## 11.7 Expected Procedural Related Events

Please refer to section on 4 for expected procedural side effects.

## 11.8 Seriousness

All events will be assessed for seriousness as defined for a SAE in section 11.1

## 11.9 Procedures for Recording and Reporting Serious Adverse Events

All serious adverse events (SAEs/SARs/SUSARs) will be recorded in the medical records and the CRF, and the sponsor's AE log. The CRF AE log of SAEs will be reported to the sponsor at least once a year.

All SAEs will be recorded from consent FPFV to LPLV. The LP will be optional to participants if they agree to undergo an LP at visit 7, day 279 the CSF sample will be sent for analysis and they will receive a safety telephone call within 5 days of visit 7 to record AEs.

All SAEs must be recorded on a serious adverse event (SAE) form. The CI/PI or designated individual will complete the sponsor's SAE form and the form will be preferably emailed to the Sponsor [[contact]](mailto:[contact]) and/or faxed on [name], within 24 hours of them becoming aware of the event. The CI/PI will respond to any SAE queries raised by the sponsor as soon as possible.

Completed SAE forms must be sent within 24 hours of becoming aware of the event to the Sponsor

**Email forms to [[contact]](mailto:[contact])**

**and/or**

**Fax forms to [name]**

# Flow Chart for SAE reporting

v2.0 18.07.16

[figure not shown]

### 11.10 Reporting SUSARs

The sponsor will notify the main REC and Medicines and Healthcare products Regulatory Agency (MHRA) of all SUSARs. SUSARs that are fatal or life-threatening must be notified to the MHRA and REC within 7 days after the sponsor has learned of them. Other SUSARs must be reported to the REC and MHRA within 15 days after the sponsor has learned of them.

### 11.11 Development Safety Update Reports (DSUR)

The sponsor will provide the main REC and the MHRA with Development Safety Update Reports (DSUR) which will be written in conjunction with the trial team and the Sponsor's office. The report will be submitted within 60 days of the Developmental International Birth Date (DIBD) of the trial each year until the trial is declared ended. This will be completed in accordance to the latest version of the Sponsor's SOP (JRO/INV/S17).

### 11.12 Pregnancy

Ambroxol crosses the placental barrier. Animal studies do not indicate direct or indirect harmful effects with respect to pregnancy, embryonal/foetal development, parturition or postnatal development. Extensive clinical experience after the 28th week of pregnancy including a clinical trial at high dose has shown no evidence of harmful effects on the foetus. The use of IMP containing ambroxol in pregnancy is not recommended; please refer to the latest version of the SmPC. Any pregnancy that occurs in a female trial subject during a clinical trial should be followed to termination or to term.

If a female participant or the female partner of a male participant becomes pregnant at any point during the trial, a completed trial specific Pregnancy Reporting Form will be emailed to the Sponsor [[contact]](mailto:[contact]) and/or faxed on **[name]**, within 24 hours of his /her becoming aware of the event in line with the Sponsors SOP (JRO/INV/S05/S06). The CI/PI will respond to any queries raised by the sponsor as soon as possible.

Completed Pregnancy Reporting Forms must be sent within **24 hours** of becoming aware of the event to the Sponsor  
**Email forms to [[contact]](mailto:[contact])**  
**and/or**  
**Fax forms to [name]**

### 11.13 Reporting Urgent Safety Measures and other Safety Events

If any urgent safety measures are taken the CI/ PI shall immediately and in any event no later than 3 days from the date the measures are taken, give written notice to the MHRA, the relevant REC and Sponsor of the measures taken and the circumstances giving rise to those measures.

### **11.14 Notification of Deaths**

All deaths, including deaths deemed unrelated to the IMP, if they occur earlier than expected will be reported to the sponsor.

### **11.15 Notification of Serious Breaches to GCP and/or the protocol**

A “serious breach” is a breach which is likely to affect:

- (a) the safety or physical or mental integrity of the participants of the trial; or
- (b) the scientific value of the trial.

The sponsor of a clinical trial shall notify the licensing authority in writing of any serious breach of:

- (a) the conditions and principles of GCP in connection with that trial; or (b) the protocol relating to that trial, as amended from time to time, within 7 days of becoming aware of that breach.

The sponsor will be notified immediately of any case where the above definition applies during the trial conduct. The sponsor’s SOP on the ‘Notification of violations, urgent safety measures and serious breaches’ will be followed.

### **11.16 Clinical Incidental Findings**

Participants that undergo any of the clinical investigations during the course of the study which may result with a “clinically significant” finding will be excluded from taking part in the study and this judgement will be made by the treating clinician. All clinical incidental findings will be considered AEs and assessed as per section 11.0. Participants with such findings that may require further investigation will be informed of the findings by the Investigator and their GP will be informed, with the participant’s consent.

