#### **7.4 Participant Exclusion Criteria**

Participants are excluded from participating in this study if 1 or more of the following criteria are met:

1. Current treatment with anticoagulants (e.g. warfarin) that might preclude safe completion of the lumbar puncture and in the opinion of the Investigator;
2. Current use of investigational medicinal product or participation in another interventional clinical trial or who have done so within 30 days prior to the first dose in the current study;
3. Exposure to more than three investigational medicinal products within 12 months prior to the first dose in the current study;
4. Confirmed dysphagia that would preclude self-administration of ambroxol up to 7 tablets TID for the duration of day 1 to day 186);
5. Significant known lower spinal malformations or other spinal abnormalities that would preclude lumbar puncture;
6. History of known sensitivity to the study medication, ambroxol or its excipients (lactose monohydrate, granulated microcrystalline cellulose, copovidone and magnesium stearate) in the opinion of the investigator that contraindicates their participation;
7. History of known rare hereditary disorders of galactose intolerance, Lapp lactase deficiency or glucose-galactose malabsorption;
8. Evidence or history of hypersensitivity to lidocaine or its derivatives;
9. History of drug abuse or alcoholism in the opinion of the Investigator that would preclude participation in the study;
10. Donation of blood (one unit or 350 ml) within three months prior to receiving the first dose of the study drug;
11. Pregnant or breastfeeding;
12. All participants of child bearing potential in the opinion of the Investigator that would preclude participation in the study and who do not agree to use double-barrier birth control or abstinence while participating in the study and for two weeks following the last dose of study drug;
13. Any clinically significant or unstable medical or surgical condition that in the opinion of the PI or PI-delegated clinician may put the participant at risk when participating in the study or may influence the results of the study or affect the participant's ability to take part in the study, as determined by medical history, physical examinations, electrocardiogram (ECG), or laboratory tests.  
Such conditions may include:
  - a) Impaired renal function
  - b) Moderate/Severe hepatic impairment

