#### **8.6.6 Electrocardiogram (ECG) Procedure**

A standard 12-lead ECG single read will be conducted at selected study visits. Prior to the assessment the participant should be rested in a supine position for 10 minutes.

If any ECG finding that is judged by the site investigator as a clinically significant change (worsening) compared with Visit 3, Day 1 (baseline, pre-dose) value will be considered an

adverse event, recorded on the source documentation and the CRF. If results are abnormal repeat testing may be performed and checked by the CI/PI or PI-delegated clinician.

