| 2                      | 8-14   | 120 mg TID                             | 360                                     | 2                                | 6                                     |
| 3                      | 15-21  | 180 mg TID                             | 540                                     | 3                                | 9                                     |
| 4                      | 22-28  | 300 mg TID                             | 900                                     | 5                                | 15                                    |
| 5                      | 29-186 | 420 mg TID                             | 1260                                    | 7                                | 21                                    |

Dose reductions are not planned but may be permitted. The PI may allow a dose reduction if adverse symptoms have emerged since dose increase that are considered to be due to the increase, are not SAEs and do not require the participant to be withdrawn, and in the opinion of the PI and participant to warrant a reduction to the last tolerated dose level.

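### Section 11.16 makes exclusion mandatory for any clinically significant finding at any time in the study, on the treating clinician's judgement, and contradicts the protocol's own withdrawal, discontinuation and eligibility rules

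*Protocol*

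**What the plan says.** Section 11.16 covers incidental findings. Its scope is set by its opening words: "Participants that undergo any of the clinical investigations during the course of the study which may result with a". The trigger named there is a result of clinical significance, and the consequence is put this way: "finding will be excluded from taking part in the study and this judgement will be made by the treating clinician". The next sentence reads "All clinical incidental findings will be considered AEs and assessed as per section 11.0". The section also provides for telling the participant and, with consent, the GP about findings that may need further investigation.

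Other parts of the protocol deal with the same kind of event:

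- Section 10.12 gives, among reasons that a withdrawal may include, "Occurrence of an AE or change in medical status or an incidental finding that leads the Investigator concerned about the participant's welfare". A withdrawn participant is asked to attend the early termination visit, if applicable.
- The section 3 risk table says that participants may be withdrawn after a serious adverse event, on the PI's opinion.
- Section 10.11 says that individuals may be discontinued from treatment after an unexpected, significant or unacceptable adverse event that the Investigators think puts safety at risk.
- Section 10.14 lists the reasons for ending drug and all assessments: withdrawal of consent, inability to continue or loss to follow-up, and death. Return to drug or assessments is then barred.
- Exclusion criterion 13 in section 7.4 covers a clinically significant or unstable condition that "in the opinion of the PI or PI-delegated clinician may put the participant at risk when participating in the study", or that may influence the results or the ability to take part.
- Section 8.4 allows one re-screening when an abnormal value may normalise, in the Investigator's opinion.

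**The concern.** Section 11.16 reads as an eligibility rule, but its wording reaches the whole study. Followed literally after the first dose, it turns a clinically significant laboratory, vital-sign or examination finding into compulsory exclusion. Elsewhere the protocol leaves the matter to the judgement of the Investigator or PI.

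Two outcomes are exposed. Laboratory data, examinations and ECG are themselves secondary safety outcomes (13.2), so the measures that assess safety would also decide who stays. The primary outcome concerns CSF penetration, with GCase activity and ambroxol level as its parameters (13.1), and it depends on a lumbar puncture at the end of treatment. Staff applying 11.16 and staff applying 10.12 could treat the same finding differently, and who remains would then depend on which section was read.

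**Working it through.** The protocol states no figure on this point, so nothing can be reproduced. The check is a comparison of the sections.

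**Step 1. Obligation, trigger and decision-maker.**

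| Section | Trigger | Consequence | Who decides |
|---|---|---|---|
| 11.16 | clinically significant finding, any clinical investigation | exclusion, mandatory | treating clinician |
| 10.12 | AE, change in medical status or incidental finding causing concern for welfare | possible withdrawal | Investigator |
| 3 (risk table) | serious adverse event | possible withdrawal | PI |
| 10.11 | unexpected, significant or unacceptable AE putting safety at risk | possible discontinuation of drug | Investigators |
| 10.14 | three listed reasons, none of them a finding as such | end of drug and all assessments | Investigator |
| 7.4, criterion 13 | clinically significant condition carrying risk or influence on results | not eligible | PI or delegate |
| 8.4 | abnormal screening value that may normalise | re-screening once | Investigator |

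The sharpest conflict is between 11.16 and the risk table: a finding that need not be serious leads to compulsory exclusion, while a serious adverse event leads only to possible withdrawal. The most direct conflict is with 10.12, which names incidental findings expressly, attaches a condition, and leaves the decision open.

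**Step 2. Timing.** Section 11.16 applies during the course of the study. Sections 10.7 (misplaced or wrongly used drug) and 10.8 (consistent dosing times) use the same phrase for the dosing period. Nothing in 11.16 restricts it to the time before the first dose.

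**Step 3. The screening-only alternative.** Suppose 11.16 covers screening alone. Section 8.4 then allows a second attempt after an abnormal value, while 11.16 offers none. Criterion 13 requires risk or influence on the study and is judged by the PI or a delegate, while 11.16 requires neither and names the treating clinician. The sections still disagree.

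**Step 4. Meaning of excluded.** Section 10.12 concerns stopping the drug and asks withdrawn participants for an early termination visit. Section 10.14 ends drug and all assessments, with no return. Section 11.16 does not say which applies.

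**Step 5. What exclusion on treatment would cost.** Visits 4 (days 9-11) and 5 (day 93) include examinations, vital signs and routine bloods (9.8, 9.18). Lumbar punctures are at screening visit 2, at visit 6 (day 186), and optionally at visit 7 (8.6.7.1), so visit 6 gives the only scheduled on-treatment CSF sample. A participant excluded at visit 4 misses visits 5 and 6; one excluded at visit 5 misses visit 6. The early termination visit uses the visit 7 procedures (9.22), which include examinations, vital signs, ECG, routine bloods and AE review, but its lumbar puncture needs separate agreement. The baseline CSF sample may then have no on-treatment partner. Section 13.3 replaces withdrawn participants, up to two per genotype group, which adds new participants but does not restore those data.

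**The case against.** The best defence is that 11.16 was meant for screening. Being excluded from taking part is eligibility language, criterion 13 uses the same clinical term, and AEs are recorded from consent, so a screening finding can be both an AE and within the course of the study. This reading is plausible. But 11.16 does not state it, and Step 3 shows that it leaves a conflict.

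A reader might infer that the rule removes the safety signal, or ends follow-up of the finding. The documents do not support that. Section 11.16 records the finding as an AE, 10.12 asks for an early termination visit, and 9.24 allows unscheduled visits to follow up AEs. What may be lost is later on-treatment observation and CSF. Whether excluded participants stay in the safety analysis may be settled in the statistical analysis plan, which is not at hand.

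A reader might also cite two further contradictions, and both are indirect:

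- Section 8.6.6 treats an ECG change "judged by the site investigator as a clinically significant change (worsening) compared with Visit 3, Day 1" as an adverse event. An event can be an AE and also lead to exclusion. Section 2.2 speaks of ECGs at each study visit, but the visit lists and Appendix 1 show none at visits 4 and 5. At visit 6 the ECG falls at the same visit as the lumbar puncture.
- Section 10.7 says "The PI may allow a dose reduction if adverse symptoms have emerged since dose increase", but only for symptoms that do not require withdrawal, so it gives way to any withdrawal rule.

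The conflict over who decides is possible rather than certain, since section 8.1 says that the treating clinician may also be an investigator. Nor should a count of excluded participants be inferred: any rate would be invented.

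**Conclusion.** The inconsistency stands. Section 11.16 makes exclusion mandatory, without a time limit and on the treating clinician's judgement, where 10.12, 10.11 and the section 3 risk table leave the matter to the Investigators or the PI, and 10.14 does not list it. A screening-only intention would lessen the consequences but not remove the conflict, because 8.4 and criterion 13 also differ.

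The consequence is conditional. If 11.16 is applied as written after the first dose, a participant excluded at visit 4 or 5 loses later on-treatment safety visits and, unless the optional lumbar puncture is accepted, any CSF sample to compare with baseline. The size cannot be given, because the protocol states no rate of clinically significant findings. The point should be corrected because it affects who stays in a trial of 20 participants, but it does not show that safety events would go unrecorded.

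**What to change.** Reconcile section 11.16 with the section 3 risk table, sections 8.4, 10.11, 10.12 and 10.14, and exclusion criterion 13, so that they agree on four matters:

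- (a) whether 11.16 applies to screening findings only or also after the first dose;
- (b) whether exclusion is mandatory or discretionary;
- (c) who decides;
- (d) whether excluded means stopping the drug, as in 10.12, or ending all assessments, as in 10.14.

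Which clinical rule to adopt is the sponsor's choice, and none is proposed here. The existing sentence that records these findings as AEs already covers recording of the event. The cost is a wording amendment to 11.16, with cross-references where needed, and no new visits, procedures or data.
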